#### Implementation outcome framework

2.8.4

Implementation outcomes will be assessed using the Proctor et al. (13) taxonomy, including acceptability, adoption, appropriateness, feasibility, fidelity, penetration, cost (incremental cost per woman counselled; see Section 2.8), and sustainability (including ASHA intention to continue beyond the study period).

### Incremental cost analysis

2.9

An incremental cost analysis will be conducted from the health system perspective to estimate the additional cost of delivering C-COMPASS per woman counselled, compared to routine postnatal care. A full cost-effectiveness analysis will not be undertaken at this stage, as reliable effectiveness estimates and utility-based outcomes (e.g., QALYs or DALYs) are not yet available. The analysis is intended to inform programmatic decision-making by estimating the additional resources required for implementation.

Three cost components will be included.
First, ASHA time costs per case will be estimated based on self-reported time spent on each contact (72 h visit, Day 7 telephone call, Day 14 visit, and Day 42 visit), multiplied by an imputed hourly rate derived from the average monthly ASHA incentive.Second, direct ASHA costs will include out-of-pocket expenditures such as transport and printed materials incurred during service delivery.Third, programme-level costs will include ASHA training costs (trainer time and ASHA participation time, amortised over three years and allocated per expected annual caseload), CHO supervision time, nurse/ANM time for activities and any additional printing or documentation costs.The primary cost metric will be the incremental cost per woman counselled (INR). Secondary cost indicators will include cost per woman screened positive for depression and cost per referral completed. Cost data will be collected using a structured costing tool administered to ASHAs and CHOs at the end of the study period. Routine care costs in control blocks will be estimated to provide comparative context. All costs will be reported in 2026 Indian Rupees (INR), and no discounting will be applied given the short study duration. Findings will be interpreted in relation to existing benchmarks for community-based mental health interventions in low- and middle-income settings to support policy relevance.

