## Introduction

1

Stillbirth, defined by the World Health Organization as foetal death at 28 or more completed weeks of gestation, remains one of the most prevalent yet under-addressed outcomes in global maternal and newborn health. An estimated 1.9 million stillbirths occur annually, with over three-quarters concentrated in sub-Saharan Africa and South Asia (1). India alone contributes approximately 460,000 stillbirths each year (2, 3), accounting for nearly one-quarter of the global burden, despite substantial progress in reducing maternal and neonatal mortality over the past decade (2, 3).

**Table 1 T1:** C-COMPASS contact schedule.

Contact	Timing	Mode	Core components
Contact 1: Early follow-up	Within 72 h of discharge	Telephone call (≥10 min)	Emotional check-in; follow-up on lactation/breast health; direct enquiry for self-harm (using scripted probe); red-flag screening
Contact 2: Check-in	Day 7 (±1 day)	Telephone call	Emotional acknowledgement and active listening; guidance on lactation suppression; assess bleeding, fever and breast pain; family engagement; provide Tele-MANAS helpline information ([name]); confirm Day 14 visit
Visit 1: Recovery	Day 14 (±2 days)	In-person home visit	First in-person visit after two telephonic counselling sessions; assess physical recovery and grief; breast health check; **Circle 1-** Heart/Feelings; **Circle 2:** Mind/Positive Thinking; family counselling; initiation of contraceptive counselling; identify and refer red flags
Visit 2: Continued recovery	Day 21 (±2 days)	In-person home visit	Assess recovery; check for physical and emotional signs of grief and breast engorgement; reinforce family support; counsel on pregnancy spacing; identify women needing further support from district psychiatrist
Contact 3: Postpartum review	Day 42 (±2 days)	Telephone call	Postpartum evaluation; follow-up on emotional wellbeing; precise contraceptive counselling; preconception planning; update ASHA registers; **Circle 3-Support** and update ASHA registers.

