#### C-COMPASS comprises four structured contacts across the 42-day postpartum period

2.6.2

Table 2.

**Table 2 T2:** Incremental cost analysis- components, data sources, and collection methods.

Cost component	Unit	Data source	Method of estimation
ASHA time: Contact 1 (≤72 h)	Minutes per case	ASHA self-report (end of study)	Time × imputed hourly rate
ASHA time: Day 7 call	Minutes per case	ASHA self-report	As above
ASHA time: Visit 2 (Day 14)	Minutes per case	ASHA self-report	As above
ASHA time: Visit 3 (Day 21)	Minutes per case	ASHA self-report	As above
ASHA time: Contact at 42 days	Minutes per case	ASHA self-report	As above
ASHA transport cost	INR per case	ASHA self-report	Direct expenditure
Printed materials/IEC	INR per case	Programme records	Procurement records
ASHA training (amortised)	INR per case	District records	Total training cost ÷ 3 yrs ÷ annual cases
CHO supervision time	INR per case	CHO self-report	Time×CHO salary rate
Routine care cost (control arm)	INR per case	Control block CHO records	Existing per-woman postnatal expenditure

**Table 3 T3:** Detailed framework selection processes.

SELECT-IT purpose	TMF selected	TMF not selected	Key attribute rationale	Practical consideration
Guiding identification of determinants (barriers/facilitators)	TDF (Theoretical Domains Framework)	CFIR (Consolidated Framework for Implementation Research)	TDF focuses on individual-level behaviour change, aligning with ASHA delivery processes; however, it does not fully capture system-level barriers. Both frameworks are evidence-based.	The study team has qualitative and implementation science expertise and can be using this TDF.
Guiding design and adaptation of strategies	ERIC Taxonomy (Expert Recommendations for Implementing Change)	Implementation Mapping	ERIC provides 73 clearly defined, operationalised strategies with standardised labels and action verbs, enabling direct application in ASHA training and CHO supervision. It has strong alignment with behaviour change evidence. Implementation Mapping was considered more resource intensive.	ERIC tools are readily available and usable without extensive training. Strategies can be directly linked to determinants identified during co-design.

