#### Reporting, documentation, and ASHA training

2.6.4

ASHAs will document the stillbirth notification date, visit dates, support provided, red flags identified, and referrals made in an additional C-COMPASS column integrated into existing ASHA registers.

CHOs will compile and report monthly summaries, including total stillbirths, number counselled, and number referred, to the Primary Health Centre (PHC). These indicators will be incorporated into routine postnatal care (PNC) reporting systems, requiring no additional data platform.

ASHA training will be conducted as a structured half-day session covering the 3-Circle Healing Model, use of scripted counselling approaches (including direct enquiry for self-harm), identification of red flags, referral pathways, and documentation procedures. Training will be delivered by CHOs across both intervention blocks prior to implementation.

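### ASHA minutes, transport spending and CHO supervision time in the primary cost metric come from one end-of-study self-report, up to about 6–7 months after the earliest contacts

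*Protocol article*

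**What the plan says.** Section 2.9 states: "The primary cost metric will be the incremental cost per woman counselled (INR". On the largest set of inputs it says that "ASHA time costs per case will be estimated based on self-reported time spent on each contact", multiplied by an imputed hourly rate. On timing it says: "Cost data will be collected using a structured costing tool administered to ASHAs and CHOs at the end of the study period".

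Table 2 agrees. The Contact 1 row gives its source as "ASHA self-report (end of study". The other four contact rows and the transport row give ASHA self-report, and the supervision row gives "CHO self-report". The remaining three rows rest on records: printed materials on programme records, training on district records ("Total training cost ÷ 3 yrs ÷ annual cases"), and routine care on control-block CHO records.

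Section 2.6.4 sets up a record kept during delivery: "ASHAs will document the stillbirth notification date, visit dates, support provided, red flags identified, and referrals made", in a new C-COMPASS column of the ASHA register. Neither duration nor expense is among the listed fields. Section 2.6.3 mentions a CHO supervision checklist used monthly.

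The list of contacts in Section 2.9 omits the Day 21 visit that Table 2 costs. The count of five contacts used here is Table 2's.

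**The concern.** The plan asks an ASHA, once and at the end, how many minutes she spent on each of several separate phone calls and home visits, and what she spent on travel. Some of these took place half a year earlier. Yet she is already keeping a register column that records the dates and content of those contacts. The article describes no time log, time-and-motion sample or other check on the recalled minutes.

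The Discussion presents cost in INR per woman counselled as the figure that government decision-makers need before adoption, and says it will show whether C-COMPASS falls within ₹200–500 per beneficiary. An error in minutes that ASHAs share passes in proportion into the ASHA time cost and does not average out over women. The limitations (Section 3.1) acknowledge social desirability in self-reported implementation metrics but do not mention recall in the cost data. Durations not recorded when the contact takes place cannot be recovered later.

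**Working it through.** The article gives no cost, minutes, hourly rate or recall interval, so there is no figure of its own to reproduce.

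**Share of inputs that are self-reported (Table 2).** Five contact times + transport + CHO supervision = 7 of 10 rows.

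**Longest recall interval (Section 2.4: post-intervention period May–November 2026, about 26 weeks; data collection completed by December 2026).** At 30.44 days per month:

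| First contact | Costing interview | Days | Months |
|---|---|---|---|
| 31 May | 30 Nov | 183 | 6.0 |
| 15 May | 30 Nov | 199 | 6.5 |
| 1 May | 30 Nov | 213 | 7.0 |
| 31 May | 31 Dec | 214 | 7.0 |
| 1 May | 31 Dec | 244 | 8.0 |

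About 6–7 months is a fair maximum, and 8 is the extreme.

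**Mean interval for Contact 1.** Assume births spread evenly over 182 days, Contact 1 three days after birth, and the interview x days after week 26. Then lag = 182 + x − (birth day + 3).

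- x = 0: lags run from 179 to 0 days; mean 89.5 days = 2.9 months. Share older than 3 months (91.3 days): (179 − 91.3)/179 = 49%.
- x = 31: lags run from 210 to 28 days; mean 119 days = 3.9 months. Share older than 3 months: (210 − 91.3)/182 = 65%.

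Later contacts are more recent: for Day 42 the same method gives means of 2.3 and 2.8 months.

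**Number of entries involved.** Section 2.12 expects about 56 women per arm after the start: 56 × 5 = 280 contacts.

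**Cases per ASHA.** Section 2.1 gives 1,019 ASHAs in six blocks. Assuming equal blocks, 1,019/6 × 2 = about 340 in two blocks, and 56/340 = 0.16 women per ASHA. Most delivering ASHAs would recall a single case.

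**Effect on the metric (illustrative only).** If contact time makes up share s of the metric and recalled minutes are off by a common fraction e, the metric moves by s × e. The article gives neither. For s = 25–75%, e = 20% moves it by 5–15%, and e = 50% by 12.5–37.5%.

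**The case against.** **Contact time may be a modest share of the cost.** Section 2.9 includes ASHA time spent in training, amortised over three years. Take 340 ASHAs, a half-day of 4 h (assumed length; Section 2.6.4 says half-day) and 9.2 × 12 = 110 cases a year. Training is then 340 × 4 / 3 / 110 = about 4.1 ASHA-hours per case. If the five contacts total 1.5–3 h (assumption), contact time is 1.5/5.6 to 3/7.1, or 27–42% of ASHA hours, before other costs are added. With the full-day training in Section 2.6.3 (8 h assumed), it is 1.5/9.7 to 3/11.2, or 15–27%. This stands. It means that taking half the cost as contact time and a 30% error (0.5 × 30% = 15%) probably overstates the shift.

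**Register entries are also self-report.** True, and they remain open to social desirability. A same-day entry nevertheless removes months of recall.

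**One bereavement may be memorable.** It may be, as an event. The article gives no reason to expect the minutes of each separate call and visit to be equally well remembered.

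**The authors keep documentation light on purpose.** They do, and this limits how much should be added. One or two short entries in a column already being introduced is a small addition.

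**Stronger readings that the document does not support.** A reader might infer that Contact 1's duration, given in Table 1 as "Telephone call (≥10 min", is not captured or cannot be checked. Table 2 does capture it, by later self-report, and the operational definitions of implementation outcomes are in a supplementary table not at hand. A reader might also infer that recall will return the scripted duration. Nothing in the article shows this, and four of the five contacts have no stated duration to drift towards. Nor do CHOs recall minutes per contact: they report supervision time. That the register column is completed at each contact is a reasonable inference from its fields, not something the article states.

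**Conclusion.** The point holds as a measurement weakness in a secondary objective. The plan fixes a single end-of-study self-report for seven of Table 2's ten rows. The lag is up to about 6–7 months and averages about 3–4 months for Contact 1, given even recruitment and an interview between week 26 and one month later. The ASHA time, transport and supervision parts of the primary cost metric therefore carry recall error that could be avoided. Its direction is unknown. Its size cannot be computed from the article, and any percentage shift is illustrative. The metric rests on recall in part, not as a whole, because training and printed materials come from records. The primary EPDS analysis is not touched. The change is worth making before contacts begin, because it is cheap and the data cannot be reconstructed afterwards.

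**What to change.** - In Section 2.6.4, add two entries to the C-COMPASS register column, completed at each contact: minutes spent and transport cost.
- In Table 2, name these entries as the data source for the five ASHA-time rows and the transport row.
- Have CHOs note supervision minutes on the monthly checklist they already use, and name it as the source for the supervision row.
- In Section 2.9, keep the end-of-study costing tool only to fill gaps.

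The cost is a few seconds of ASHA documentation at roughly 280 contacts, plus a line in the training. The entries remain self-report, so the caution about social desirability in Section 3.1 should be extended to the cost data.

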#### Intervention deliverers

2.6.1

The intervention will be delivered by Accredited Social Health Activists (ASHAs), with support from the study team supervisors. ASHAs were selected as the primary implementers as they are trained under the National Health Mission (NHM) and function as the first point of contact between communities and the formal health system.

ASHAs are already mandated to conduct postnatal home visits under the Home-Based Newborn Care (HBNC) programme. C-COMPASS does not require the introduction of a new cadre of workers or additional visits beyond the existing postnatal care schedule. Instead, it integrates a structured counselling protocol, targeted training, and a defined referral pathway into routine ASHA-led visits. This design enhances feasibility and scalability by leveraging existing health system infrastructure and enables assessment of whether structured psychosocial support following perinatal loss can be delivered within the current system at marginal additional cost.

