### Block selection and matching

2.7

Four of the six SHRiSTI-surveilled blocks will be purposively selected: two allocated to the intervention arm (receiving C-COMPASS from May 2026) and two to the control arm (routine postnatal care). Block pairs will be matched based on population size, ASHA density, monthly stillbirth volume from SHRiSTI surveillance, distance to district referral facilities, and absence of any co-occurring community mental health programme.

Women in the control blocks will receive routine postnatal care as currently delivered within the National health mission program, without any C-COMPASS protocol, training, or structured referral pathway. In practice, ASHA postnatal visits in this context are designed for women with live births and focus on newborn care and breastfeeding support; no standardised protocol, training, or referral pathway exists for ASHA-delivered emotional support following stillbirth. Evidence from qualitative research conducted in the same district using a social autopsy lens found that postnatal support for bereaved women is largely informal and inconsistent, with women commonly discharged from facilities within 24–48 h with minimal counselling and returning to home environments where grief is frequently met with social silence or pressure rather than structured acknowledgement (8). No scripted emotional support, self-harm enquiry, lactation suppression guidance, or structured psychological referral pathway is routinely activated following stillbirth in the control blocks. The Tele-MANAS helpline is available as national infrastructure but is not routinely provided to bereaved women in current practice. The control condition thus represents the documented current standard of care in this setting, against which the incremental effect and cost of C-COMPASS will be estimated.

The remaining two blocks, under SHRiSTI project, will be excluded to minimise contamination, address time and resource constraints, and allow their use as potential future comparators.

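### As described, the cost analysis yields a largely gross cost of C-COMPASS, not the promised increment over routine care, and the two arms' cost sources are not matched

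*Protocol article*

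**What the plan says.** **The promise.** The secondary objectives (2.3.1.2) include the incremental cost per woman counselled relative to routine care. Section 2.9 opens with the aim to "estimate the additional cost of delivering C-COMPASS per woman counselled, compared to routine postnatal care". Section 2.7 names the control condition as the comparator for both effect and cost.

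**The method.** Section 2.9 lists three components: ASHA time, direct ASHA costs and programme-level costs.
- On the first: "ASHA time costs per case will be estimated based on self-reported time spent on each contact", "multiplied by an imputed hourly rate derived from the average monthly ASHA incentive".
- On the control blocks: "Routine care costs in control blocks will be estimated to provide comparative context".
- No formula for the increment is given.

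**The sources.** Table 2 takes intervention ASHA time and transport from ASHA self-report. Its control-arm row takes routine care cost from control-block CHO records, with the method given as "Existing per-woman postnatal expenditure".

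**What routine care already contains.** Section 2.6.1 says "C-COMPASS does not require the introduction of a new cadre of workers or additional visits beyond the existing postnatal care schedule". The Discussion adds that C-COMPASS gives structure to a visit ASHAs already make after a stillbirth. Section 2.7, on the other hand, says that "ASHA postnatal visits in this context are designed for women with live births and focus on newborn care and breastfeeding support".

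**The concern.** An incremental cost is the cost with the intervention minus the cost that would have arisen without it. If C-COMPASS sits inside visits that already take place, some of the ASHA minutes and travel counted in 2.9 would have been spent anyway. Adding them up in full then answers a different question: what the contacts cost, not what they add.

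The figure carries weight. The Discussion sets it against a range of ₹200–500 per beneficiary and presents it as what government needs before considering adoption. Section 3.2 makes it the economic argument for scale-up. It is also the natural test of the claim that C-COMPASS adds no visits, and that test needs ASHA time after stillbirth in the control blocks, measured as it is in the intervention blocks.

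**Working it through.** The documents give no cost result and no cost formula, so there is no figure of the plan to reproduce. The check sets the sections side by side and then uses algebra to see when gross and incremental cost differ.

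**1. Which items are increments?**
- ASHA training and additional printing or documentation arise only with C-COMPASS. They are increments as listed.
- ASHA contact time and transport are entered in full, with no deduction for routine visits. By 2.6.1 and the Discussion, part of this would occur under routine care. As listed, they are gross.
- The control-block cost is given a contextual role in 2.9 and a row in Table 2. Neither place says that it is subtracted.

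**2. Gross against increment.** Let T be the cost of ASHA contact time and transport, and P all other components, taken here as wholly additional. Let s be the share of T that routine care would use anyway, and a = T/(T + P).

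- Gross: G = T + P
- Increment: I = T(1 − s) + P = G(1 − a·s)
- Ratio: G/I = 1/(1 − a·s)

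Neither a nor s is in the documents. Illustrative assumptions are a = 0.3 to 0.7 and s = 0.25 to 0.75.

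| a | s | a·s | G/I | Increment behind a gross cost of ₹500 |
|---|---|---|---|---|
| 0.3 | 0.25 | 0.075 | 1/0.925 = 1.08 | 500 × 0.925 ≈ ₹463 |
| 0.3 | 0.75 | 0.225 | 1/0.775 = 1.29 | 500 × 0.775 ≈ ₹388 |
| 0.7 | 0.25 | 0.175 | 1/0.825 = 1.21 | 500 × 0.825 ≈ ₹413 |
| 0.7 | 0.75 | 0.525 | 1/0.475 = 2.11 | 500 × 0.475 ≈ ₹238 |

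If s = 0, then G = I and there is no error. Section 2.7 makes a low s conceivable, because routine visits are built around live births. Section 2.6.1 and the Discussion point to a higher s.

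**3. Effect on the ₹200–500 comparison.** An increment exactly at ₹500 corresponds to a gross cost of 500/0.925 ≈ ₹541 at the mild end of the assumed range and 500/0.475 ≈ ₹1,053 at the other. A gross figure could therefore lie above the range while the increment lies within it.

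**4. Would subtracting the Table 2 control figure repair this?** Call that figure C. Then G − C = I only if C = s·T, that is, only if C measures the ASHA time and transport that routine care spends on women after a stillbirth, valued in the same way. Table 2 does not secure this. One arm is built up from ASHA-reported minutes and outlays. The other comes from CHO records of postnatal expenditure per woman, with no stated restriction to stillbirth. The difference could err in either direction.

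**The case against.** The strongest reply is that subtraction is intended. The objective, the opening of 2.9 and section 2.7 all name routine care as the comparator, and Table 2 lists the control-arm cost among the components of an incremental analysis. An article may also leave the arithmetic and the content of the costing tool to a fuller document. This stands in part. A reader might infer that the primary metric is definitively a gross cost with control data used for nothing but background, and the documents do not go that far. They leave the subtraction unstated, and the contextual role given to control cost in 2.9 sits badly with 2.7.

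Three further points limit the concern:

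- A reader might infer that control costs come from women with live births. The Table 2 row is labelled as control arm and per case, and it does not say which women. What can be said is that it is not stated to be specific to stillbirth.
- A reader might infer that all contact time is counted throughout. That is true of Table 2, but the contact list in the text of 2.9 omits the Day 21 visit.
- The costing tool is to go to ASHAs and CHOs, with no limit to intervention blocks, so some control-block ASHA data may be planned. Table 2 nevertheless names CHO records as the source for the control cost.

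Condensation does not explain what remains. The article itself fixes different sources for the two arms, and that choice prevents a like-for-like difference even if subtraction is intended.

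**Conclusion.** The point holds in a limited form. Section 2.9 and Table 2, as written, do not deliver the increment over routine care that the objective, the opening of 2.9 and section 2.7 promise. The listed procedure gives a largely gross cost, mixed with items that are true increments, and the control figure specified in Table 2 cannot be relied on to correct it.

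The size cannot be determined from the documents. It is zero if control ASHAs spend no time after a stillbirth, and it grows with the share of contact time that routine care already uses. The ratio of 1.08 to 2.11 rests wholly on assumed shares and on treating all other components as additional. Putting assumed minutes on each contact and quoting a percentage error would describe ASHA time only, not the rupee metric, which also includes training, supervision and materials.

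This concerns one secondary objective and leaves the EPDS analysis untouched. It should be corrected because the figure is meant to inform adoption.

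**What to change.** - **Define the metric.** State the primary cost metric as mean cost per enrolled woman with stillbirth in intervention blocks, minus the same mean in control blocks, divided by the proportion of intervention women counselled.
- **Match the sources.** Administer the same end-of-study costing tool to control-block ASHAs and CHOs for their enrolled stillbirth cases (number of contacts, minutes, transport), and value ASHA time at the same imputed hourly rate in both arms. Change the control row of Table 2 to match.
- **Report both figures.** Give the gross C-COMPASS cost as a secondary indicator, and say which of the two is compared with ₹200–500.
- **Reconcile the contact lists.** Make the contacts costed in the text of 2.9 agree with Table 2, which includes Day 21.

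The cost is a short extra data-collection task in the control blocks, where section 2.12 expects about 56 women in the post-intervention period. The tool is already planned for the end of the study, and no new staff should be needed.
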